### Outcome measurements

Measurement time points and questionnaires used are shown in Table 1. Data collection will take place at baseline (before the start of the intervention) and at 3, 6, and 12 months after baseline in both groups. Additional data of the intervention group will be collected at two other time points: at 3 weeks (after 6 treatments) and at 6 weeks (after 12 treatments = immediately post-treatment). Information about patient attendance and drop-out will be recorded continuously. Patients of both groups will receive the follow-up questionnaires at 3, 6 and 12 months via Internet or a paper-and-pencil version with an addressed return envelope, depending on the participant’s preference.

**Table 1 T1:** Measurements and time points

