		**Measurement time points**					
**Measure**	**Questionnaire**	**T0**	**V1**	**V2**	**T1**	**T2**	**T3**
Patients’ background (demographics, clinical)	-	X			X	X	X
CTS symptom severity and functional status	BCTQ	X	X	X	X	X	X
Quality of life	WHOQOL-BREF	X		X	X	X	X
Depression and anxiety	PHQ-4	X	X	X	X	X	X
Health related resource utilization	Non-standardized	X					X
Absenteeism from work	Non-standardized	X			X	X	X

T0 = baseline, V1 = 3 weeks (only intervention group), V2 = 6 weeks (only invention group), T1 = 3 months, T2 = 6 months, T3 = 12 months, BCTQ = Boston Carpal Tunnel Questionnaire, WHOQOL-BREF = World Health Organization Quality of Life questionnaire abbreviated version, PHQ-4 = Patient Health Questionnaire-4.

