#### Health care related resource utilization

Patients will be asked how many times they visited a professional caregiver (general practitioner, physiotherapist, psychologist, specialist, or other health care providers) in the past 12 months, if they spent time in the hospital or used medication via a non-standardized questionnaire.

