#### Planned analyses

The baseline characteristics of those who complete and will drop out during follow-up will be compared by means of an independent *t*-test for continues data and by Chi square analysis for categorical data. All analyses will be based on the intention-to-treat principle. Linear mixed effect models will be used to compare the change from baseline at 12 months between groups on the BCTQ, WHOQOL-BREF, absenteeism from work and health related resource utilization. Linear mixed effect models are able to adjust for missing values and are therefore used to avoid loss of information [27]. The baseline, three and six months measurements, as well as duration of symptoms until inclusion, age, gender, and co-morbidity will be included as covariates. Taking these covariates into account will adjust for differences within the groups and decrease variance. It will also adjust for possible baseline differences between groups [28]. When the data are normally distributed, Pearson’s correlation coefficients will be generated to examine the relationship between treatment outcome and depression and anxiety.

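### Resource use is collected only at baseline and 12 months, so the shared mixed model with 3- and 6-month covariates does not fit it, and the 12-month count leaves the study's own traction sessions undefined

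*Protocol article*

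**What the plan says.** The Planned analyses section of the protocol article assigns four outcomes to linear mixed models of change at 12 months: the BCTQ, "WHOQOL-BREF, absenteeism from work and health related resource utilization". It then gives one covariate list for all of them: "The baseline, three and six months measurements, as well as duration of symptoms until inclusion, age, gender, and co-morbidity will be included as covariates". The abstract gives the same list in slightly different form, with changes at 3 and 6 months. Planned analyses justifies the mixed model by its handling of missing values.

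Table 1 defines "T1 = 3 months, T2 = 6 months, T3 = 12 months". Its row "Health related resource utilization" is marked at T0 and T3 only. The rows for BCTQ, WHOQOL-BREF and absenteeism are marked at T1 and T2 as well.

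The section on resource utilization describes one questionnaire asking "how many times they visited a professional caregiver (general practitioner, physiotherapist, psychologist, specialist, or other health care providers) in the past 12 months", plus hospital time and medication.

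The objectives section says, directly after defining the primary outcome, that the 3- and 6-month changes in BCTQ function and symptoms will serve as covariates. On session attendance, Outcome measurements states: "Information about patient attendance and drop-out will be recorded continuously".

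**The concern.** The stated model calls for covariates that the schedule does not produce for this outcome. Whoever carries out the analysis must either leave them out or substitute something else, and the article does not say which. The choice affects what the treatment comparison means.

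Two further difficulties follow from the same schedule. The reason given for using a mixed model depends on intermediate measurements, and resource use has none. And the single 12-month recall covers the weeks of traction treatment, which bring one arm to the clinic twice a week. A comparison of visit counts then depends on whether patients include those sessions.

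The stake is a named hypothesis, that traction leads to less use of health care, on an outcome that the Discussion presents as a strength of the trial.

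**Working it through.** **1. The plan's own figure.** The article gives 64 per arm for d = 0.5, power 0.80 and two-sided alpha 0.05. The normal approximation is n = 2(1.960 + 0.842)² / 0.5² = 62.8, so 63; the exact t-test gives 63.8, so 64. The figure reproduces. It concerns the BCTQ and is not in dispute.

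**2. Schedule against model.**

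| Outcome | T0 | T1 (3 m) | T2 (6 m) | T3 (12 m) | Own 3- and 6-month covariates available? |
|---|---|---|---|---|---|
| BCTQ | X | X | X | X | yes |
| WHOQOL-BREF | X | X | X | X | yes |
| Absenteeism | X | X | X | X | yes |
| Resource use | X | – | – | X | no |

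The blanks are unlikely to be a layout fault. The neighbouring rows are intact, and a questionnaire that recalls a full year fits collection at baseline and 12 months.

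**3. Reading A: the covariates are the outcome's own values.** Two required covariates are absent for everyone, so 0 of 200 records have a complete covariate set.

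**4. Reading B: the covariates are the BCTQ changes.** The model can then be fitted. But BCTQ change at 3 and 6 months is measured after randomisation, and the trial expects traction to improve it. If fewer symptoms lead to fewer visits, adjusting for them removes that part of the effect. The 12-month count also includes care received before the 3- and 6-month forms, so the covariate can itself be a result of the care being counted.

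**5. Missing forms.** Without the 3- and 6-month covariates, each patient has one baseline and one follow-up value, and the model reduces to a baseline-adjusted comparison (ANCOVA). A patient without a T3 form adds no outcome information: in a simulated set of 200 with 36 T3 values missing, 164 were analysed. The article states no non-return rate, so the range below is an assumption. The last column is the standardised difference detectable with 80% power in an unadjusted t-test.

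| Assumed T3 non-return | Left per arm | Detectable d |
|---|---|---|
| 0% | 100 | 0.40 |
| 10% | 90 | 0.42 |
| 20% | 80 | 0.45 |
| 30% | 70 | 0.48 |

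The loss of precision is modest. The greater issue is that non-return may be selective, and this model has no intermediate resource-use data with which to allow for it.

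**6. Study sessions in the count.** Sessions planned: 2 per week × 6 weeks = 12, in the traction arm only. A completer attends at least 70%: 0.7 × 12 = 8.4, so at least 9. For a completer the count therefore differs by 9 to 12 visits between including every attended session and including none. For a control patient the difference is 0.

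**The case against.** The strongest reply is that the model can be run. The objectives section is the only place that says what the 3- and 6-month covariates are, and it names BCTQ change, which is collected at those times. That is a fair reading, though the sentence is attached to the primary outcome, and neither the abstract nor Planned analyses extends it to resource use. It removes the arithmetic obstacle but leaves the post-randomisation adjustment of step 4. The rule needs correcting on either reading.

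A reader might go further than the documents allow in four ways:

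- **That the hypothesis cannot be tested.** It can. A baseline-adjusted comparison at 12 months tests it.
- **That one missed form loses all of a patient's data for the year.** The control-group section says treatments received are documented throughout from questionnaires and medical records, and the section on demographic and clinical variables has medication verified from records. What is lost is chiefly the self-reported visit count.
- **That the gap between 64 and 100 per arm is a planned loss of 36%.** No dropout rate is stated, and that gap concerns the BCTQ. Resource use was not powered.
- **That counting the sessions would reverse the sign of the result.** The article gives no visit counts for either arm, so this cannot be shown. The researcher is described as handling the device during treatment, so some patients may not regard a session as a visit to a caregiver. The questionnaire is not shown and may already address this.

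It is also fair that a single 12-month recall is not an error. It covers the follow-up year exactly and matches the baseline window. Adding shorter recalls at 3 and 6 months is a trade-off, because their sum would be set against a 12-month baseline recall, and patients already past those time points would lack the items.

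**Conclusion.** The point holds for one secondary outcome. The covariate rule in Planned analyses does not match Table 1: the 3- and 6-month values either do not exist (0 of 200 records complete) or are post-randomisation BCTQ results that may absorb part of the effect. The missing-data argument for the mixed model does not carry over to an outcome with a single post-baseline value.

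Separately, up to 12 visits per traction patient, and none per control patient, may or may not be in the count. How far this would move the comparison is unknown without visit data.

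The conclusion assumes that Table 1 is the full collection schedule for this questionnaire and that the covariate list applies to all four outcomes, as written. The primary data schedule and the sample size are not affected. The correction should be made, but it is a small one.

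**What to change.** - **Model.** For resource use, drop the 3- and 6-month covariates. Compare 12-month use between arms, adjusted for the baseline value and the baseline covariates already listed (symptom duration, age, gender, co-morbidity).
- **Missing data.** Do not rely on the mixed model for missing T3 forms on this outcome. State how they are handled, and say which components (treatments received, medication) can be completed from medical records.
- **Study sessions.** Instruct patients on the T3 form to leave out study traction sessions. Report visit totals both without them and with attended sessions added from the attendance record. Mark any T3 forms returned before the instruction was added.
- **Optional.** Resource-use items could be added to the 3- and 6-month questionnaires to reduce dependence on one form. The trade-off over recall windows and patients already past those visits makes this a choice, not a requirement.

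The cost is analysis wording and one line of instruction on a form already in use. Attendance is already recorded, so the second total needs no new data collection.

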**Methods/Design:**

Patients diagnosed with CTS will be recruited from an outpatient neurology clinic and randomly assigned to the intervention group (mechanical traction) or the control group (care as usual). Participants in the intervention group will receive 12 treatments with mechanical traction during six consecutive weeks. Primary outcome is symptom severity and functional status, which are measured with the Boston Carpel Tunnel Questionnaire (BCTQ). Secondary outcomes are quality of life (WHOQOL-BREF), health related resource utilization, and absenteeism from work. Outcomes will be assessed at baseline, and at 3, 6, and 12 months after inclusion. Linear mixed effect models will be used to determine the change from baseline at 12 months on the BCTQ, WHOQOL-BREF, absenteeism from work and health related resource utilization. The baseline measurement, change from baseline at three and six months, as well as duration of symptoms until inclusion, age, gender, and co-morbidity will be included as covariates The Pearson’s correlation coefficient will be generated to assess the correlation between depression and anxiety and treatment outcome.

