### Hypothesis and objectives

The purpose of this study is to evaluate the effectiveness of mechanical traction in alleviating symptoms and improving hand function in patients with CTS compared to care as usual. The primary outcome is the change from baseline in symptom severity and functional status at 12 months, which is measured using the Boston Carpal Tunnel Questionnaire (BCTQ). Change from baseline in functional status and symptom severity at three and six months will be used as covariates. As secondary outcomes, we will assess quality of life, health related resource utilization, and absenteeism from work. Tertiary outcome is the impact of psychological distress on treatment outcome. We hypothesize that hand function and symptom severity will significantly improve more in CTS patients receiving 12 treatments with mechanical traction compared to CTS patients who receive care as usual after 12 months. Moreover, 12 treatments with mechanical traction will result in less absenteeism from work, a higher quality of life, and less health related resource utilization compared to care as usual in CTS patients after 12 months follow-up. Furthermore, a higher degree of depression and anxiety at baseline will result in a lower treatment effect in CTS patients.

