## Statistical analysis

### Sample size and power calculation

The sample size calculation is based on a clinically relevant improvement from baseline on the functional and symptom severity scores of the BCTQ after 12 months follow-up. Sixty-four patients need to be included per treatment arm to statistically detect a minimum effect size of *d* = 0.5 between mean BCTQ scores of both groups with a power of 0.8 and a two-sided alpha of 0.05. A total of 200 patients will be included (100 patients per treatment arm), taking into account possible drop-out.

The following outcomes are defined. A completer is a patient who participated in at least 70% of the intervention sessions and the assessments. A responder is a patient who will have a reduction of 0.74 of the mean score (minimal clinical important difference) on the BCTQ compared to baseline [21]. A drop-out is a patient with less than 70% of the intervention or the follow-up data.

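### Adjusting the 12-month comparison for 3- and 6-month outcomes means the group coefficient is not the 12-month effect that the trial hypothesises and powers

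*Protocol article*

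**What the plan says.** The article puts the intermediate results on the covariate side in three places.

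- Planned analyses: "The baseline, three and six months measurements, as well as duration of symptoms until inclusion, age, gender, and co-morbidity will be included as covariates". The quantity compared is the change from baseline at 12 months, for the BCTQ, WHOQOL-BREF, absenteeism and resource utilization.
- Hypothesis and objectives: "Change from baseline in functional status and symptom severity at three and six months will be used as covariates". The same section defines the primary outcome as change from baseline at 12 months and hypothesises greater improvement with traction at that time.
- Abstract, Methods/Design: the covariate list opens with "The baseline measurement, change from baseline at three and six months".

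Planned analyses invokes intention to treat and gives this reason for the model: "Linear mixed effect models are able to adjust for missing values and are therefore used to avoid loss of information". It justifies the covariates by lower variance and by possible baseline differences between groups.

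Sample size and power calculation requires 64 per arm for d = 0.5 "between mean BCTQ scores of both groups with a power of 0.8 and a two-sided alpha of 0.05". It then states "A total of 200 patients will be included (100 patients per treatment arm), taking into account possible drop-out".

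The intervention section has traction finishing after six weeks. Table 1 collects BCTQ, WHOQOL-BREF and absenteeism at 3, 6 and 12 months in both groups, but resource utilization only at T0 and T3.

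**The concern.** Lower variance and baseline imbalance are reasons to adjust for variables fixed before randomisation. The 3- and 6-month scores are later than that. They measure the same construct as the outcome, after the full traction course, and part of any traction effect is already in them. Holding them constant asks whether two patients with the same early response differ at 12 months by group. That is not the total effect of assignment, which is what the hypothesis, the intention-to-treat statement and the sample size all concern.

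The model also loses its repeated structure. Once the earlier visits are predictors, only the 12-month value is left as a response, one per patient per scale. At stake are the primary estimate, its power and the planned protection against missing data.

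**Working it through.** **Inputs from the article.** d = 0.5, two-sided alpha 0.05, power 0.8, 64 evaluable and 100 enrolled per arm (Sample size and power calculation).

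**Assumptions, because the article gives no values.** Outcome SD 1 at each visit. Correlation r between visits of 0.3 to 0.8, either equal for all pairs or AR(1). The main scenario is an effect of 0.5 SD at 3, 6 and 12 months.

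**1. The plan's own figure.** Normal approximation: n = 2(1.960 + 0.842)²/0.5² = 62.8, so 63. The two-sample t-test gives 63.77, so 64, with power 0.801. The stated 64 reproduces. It is for an unconditional difference between means.

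**2. What the planned model estimates.** Let S be the correlation matrix of the 0-, 3- and 6-month scores, c their correlations with the 12-month score, and b = S⁻¹c. The expected group coefficient is δ12 − b′(0, δ3, δ6). With baseline in the model, using change or score for the outcome or the early covariates gives the same group coefficient.

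- Equal correlation: each weight is r/(1 + 2r). For a constant effect the coefficient is 0.5/(1 + 2r), and the share removed is 2r/(1 + 2r).
- AR(1): only the 6-month score has weight, equal to r. The coefficient is 0.5(1 − r), and the share removed is r.

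**3. Power.** SE = √(residual variance × 2/n × V), where V = 1 + m′S⁻¹m/4 and m = (0, δ3, δ6). Power = Φ(|coefficient|/SE − 1.96). Example with equal correlation, r = 0.5, n = 64:

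- coefficient 0.5 − 0.25 × 0.5 − 0.25 × 0.5 = 0.25
- residual variance 1 − 3 × 0.5 × 0.25 = 0.625
- V = 1 + 0.5/4 = 1.125
- SE = √(0.625 × 2/64 × 1.125) = 0.148
- power = Φ(1.687 − 1.960) = 0.39

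| r | Equal: coefficient (removed) | Power, 64/arm | Power, 100/arm | Baseline-only power, 64/arm | AR(1): coefficient (removed) | Power, 64/arm | Baseline-only power, 64/arm |
|---|---|---|---|---|---|---|---|
| 0.3 | 0.31 (38%) | 45% | 63% | 84% | 0.35 (30%) | 51% | 81% |
| 0.5 | 0.25 (50%) | 39% | 56% | 90% | 0.25 (50%) | 34% | 81% |
| 0.6 | 0.23 (55%) | 39% | 56% | 94% | 0.20 (60%) | 27% | 83% |
| 0.7 | 0.21 (58%) | 42% | 59% | 98% | 0.15 (70%) | 20% | 85% |
| 0.8 | 0.19 (62%) | 48% | 67% | >99% | 0.10 (80%) | 14% | 91% |

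A simulation of 4000 trials at equal r = 0.6 and 64 per arm gave a mean coefficient of 0.23 and power of 40%, against 94% with baseline adjustment only.

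**4. Other trajectories, same range of r.**

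- Growing effect (half, then three quarters, of the 12-month effect): 23% to 39% removed under equal correlation, 22.5% to 60% under AR(1).
- Waning effect (1.4, then 1.2, times the 12-month effect), equal correlation: 49% to 80% removed.
- Early lag (−0.2 and −0.1 SD, then +0.5 SD), equal correlation: 0.5 + 0.3r/(1 + 2r) = 0.56 to 0.59, an inflated estimate.
- Benefit of 0.5 SD at 3 and 6 months, none at 12: the coefficient favours control by r/(1 + 2r) = 0.19 to 0.31 SD under equal correlation, and by 0.5r = 0.15 to 0.40 SD under AR(1).

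**5. Missing data.** With one response per scale, a patient random effect cannot be separated from the residual, and the model reduces to analysis of covariance. Without imputation, a patient needs the 3-, 6- and 12-month scores to contribute. If 10%, 15% or 20% are missing independently at each visit (assumed), 0.9³ = 73%, 0.85³ = 61% or 0.8³ = 51% have all three. A model using only baseline and 12 months would keep 90%, 85% or 80%.

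**The case against.** The strongest defence is that the article uses the word covariates loosely and means repeated measures, since the missing-data rationale only makes sense on that reading. It does not hold against the text. Three sections say the same thing, Planned analyses lists the early visits beside age and gender, and only the 12-month change is named as the quantity compared.

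Other parts of the defence stand and limit the claim.

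- A reader might infer that most of the traction effect is adjusted away. The article gives no between-visit correlations and no early effects, so that cannot be stated as fact. With equal correlation and a constant effect the share passes one half only when r exceeds 0.5, and it is smaller if the effect grows over time.
- A reader might also infer that the coefficient captures only what happens after month 6. It does not: with a constant effect nothing changes between the groups after month 6, yet the coefficient is 0.19 to 0.31 SD under equal correlation.
- Bias toward no effect is not assured, because an early lag gives inflation.
- The power figures at 64 per arm apply if attrition reaches 36 of the 100 enrolled per arm; the article states no drop-out rate.
- Patients with a missing early score are lost only if it is not imputed, and an analysis plan not shown here may provide for that.

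The covariate choice itself is not a detail left to such a plan. The article fixes it for the primary analysis.

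**Conclusion.** The covariate rule is wrong as written. The planned group coefficient is conditional on early response and does not estimate the total 12-month change that the trial hypothesises and powers. That conclusion needs no assumption about correlations.

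Its size does. For a constant 0.5 SD effect and r of 0.3 to 0.8, about 30% to 80% of the effect is removed. Power is about 14% to 51% at 64 per arm across the two correlation patterns. Under equal correlation it is 39% to 48% at 64 per arm, and still only 56% to 67% with all 100. Baseline-only adjustment keeps the full 0.5 SD and gives at least 81% at 64 per arm throughout. For other trajectories the documents support neither a fixed size nor a fixed direction.

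The reason given for using a mixed model also fails, because one response per scale remains and early missing values then cost patients unless imputed. For resource utilization, 3- and 6-month values of that outcome do not exist, so a covariate list meaning each outcome's own earlier values cannot be applied to it.

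**What to change.** Delete the 3- and 6-month values from the covariate lists in the abstract, Hypothesis and objectives, and Planned analyses.

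For the BCTQ, WHOQOL-BREF and absenteeism, make the 3-, 6- and 12-month values repeated responses in one mixed model. Include group, visit, group-by-visit, the baseline score and only the listed pre-randomisation covariates (symptom duration, age, gender, co-morbidity). Use a suitable within-patient covariance; unstructured is one acceptable choice. Take the 12-month group contrast as primary. A patient who misses one follow-up visit then still contributes the others, which is what the article wants from the mixed model.

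For resource utilization, compare the groups at 12 months with adjustment for baseline.

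The cost is analysis wording only. The data are already scheduled in Table 1, and no extra visits or patients are needed.

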### Tertiary outcome measures

#### Depression and anxiety

The four-item Patient Health Questionnaire (PHQ-4) will be used to measure self-reported depression and anxiety. The questionnaire consists of two items on depression and two on anxiety, referring to the past two weeks. A higher score represents a higher level of anxiety and depression. The PHQ-4 is a reliable instrument that has been validated in a general population [26].

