## Discussion

This paper describes the design for an RCT with the purpose to study the effectiveness of mechanical traction as a treatment for CTS compared to care as usual. Recruitment started in October 2013 in the VieCuri Medical Center in Venlo, The Netherlands. The outpatient neurology clinic registers over 400 CTS patients annually of whom about 350 will be eligible. During a period of 12 months, these patients will be invited to participate in the RCT. For several reasons, it is realistic to predict a response rate of 60%. First, the new treatment is painless and non-invasive. Second, in case of a non-responder, the patient can always make a choice for surgery without any evidence for poorer prognosis. The predicted sample size of 200 patients will easily enable the researchers in one year to include sufficient patients into the trial with sufficient power. The clinical relevance of this RCT is substantial. First, CTS is very common, not only in the general population (up to 4%), but especially in the working population (up to 10%). Secondly, because the prevalence in the working population is relatively high, CTS-related days of sick leave and workers’ compensation lead to an economic burden. Absenteeism from work after carpal tunnel release (CTR) is on average two to seven weeks [29,30]. In the US, cumulative excess loss of earnings of 4,443 workers who filed a CTS related workers’ compensation claim was estimated at $197 to $382 million over 6 years [31]. Thirdly, the long-term benefits of current treatment strategies of CTS are far from optimal. Fourth, it is well known that recovery from pain symptoms can be mediated by the patient’s mental state, especially anxiety and depression. Pain is a process from nociceptive registration to a subjective experience, which can be influenced by psychological wellbeing [32]. Depression has been reported as a predictor of pain intensity in CTS patients [6]. Research into the mediator effect of emotional distress on the outcome of CTS treatment is limited. Hobby *et al*. reported a significant association between BCTQ scores and scores on the depression and anxiety scales [33]. Moreover, Lozano Calderon *et al*. reported that patient dissatisfaction and perceived impairment after CTR can partly be predicted by depression [34]. Up until now, non-invasive CTS treatment mostly consists of splint therapy and corticosteroid injections. These treatments have not been proven to be effective in the long-term [8-10]. Invasive CTR, on the other hand, results in a positive outcome in only 70 to 75% of the patients in the long-term [16,17]. Mechanical traction using the Phystrac traction device is a promising treatment option. It is non-invasive and has been reported to result in substantial symptom relief in 70% of the patients, and in 60% of the patients two years post-treatment [19,20]. However, there is no conclusive scientific evidence for the effectiveness of mechanical traction. Therefore, there is a clear need for an RCT to compare mechanical traction to regular treatment options, such as splint therapy, steroid injections, and CTR. Improvements in functional status and symptom severity will be measured using the BCTQ. This questionnaire has been proven to be a valid and reliable outcome measure [21,22]. It is widely used in clinical practice to evaluate the recovery of CTS symptoms after treatment. This means that we have an easy, user-friendly, and quick measure to assess clinical outcome. One strength of this study is the additional outcome measures. Apart from clinical measures, quality of life, absenteeism from work, and health related resource utilization will be measured. Another strength of this study is the follow-up length. Many studies only include a few weeks or months follow-up, while the current study aims at a 12 months follow-up period. A possible limitation of this study is the heterogeneity of the care as usual group. The patients in this group can receive different forms of treatment or no treatment at all. However, since this represents the general practice in an outpatient neurology clinic, the results of this RCT will provide clinically relevant information.

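### Baseline PHQ-4, already collected before allocation is known, could join the model covariates: a free but minor gain in precision

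*Protocol article*

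**What the plan says.** In the Protocol article, Planned analyses, the linear mixed models for BCTQ, WHOQOL-BREF, absenteeism and resource use share one covariate list. It comprises the baseline, three-month and six-month measurements, "as well as duration of symptoms until inclusion, age, gender, and co-morbidity will be included as covariates". The Abstract gives essentially the same list. The section explains that the covariates are there to lower the variance and to correct for possible differences between the arms at baseline.

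PHQ-4 "will be used to measure self-reported depression and anxiety". Table 1 marks it at T0 and at every later time point. The Blinding section says that neither patient nor researcher knows the allocation during the intake, so the T0 value is a true pre-randomisation measurement.

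The article argues that distress matters. The Background and the Discussion cite depression as a predictor of pain in CTS. The Discussion adds that one study "reported a significant association between BCTQ scores and scores on the depression and anxiety scales", and that another found depression partly predictive of perceived impairment after carpal tunnel release. Under Hypothesis and objectives the expectation is that "a higher degree of depression and anxiety at baseline will result in a lower treatment effect in CTS patients".

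In the planned analyses, however, depression and anxiety appear only in a separate Pearson correlation with treatment outcome, outside the treatment model.

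**The concern.** The list has a declared purpose, and baseline PHQ-4 fits it: it is measured before allocation, it is available in both arms, and the article supports it with evidence on symptoms and outcome. For age, gender and co-morbidity, the Background speaks only to who develops CTS. For symptom duration, the article offers no evidence on outcome. A covariate with a documented rationale is therefore left out while others without one are included.

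What is at stake is precision. If baseline distress predicts the 12-month BCTQ beyond what baseline BCTQ already explains, leaving it out makes the confidence interval for the treatment effect somewhat wider than it need be. This would be given up although the data are already in hand.

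**Working it through.** **Inputs from the document.** The section Sample size and power calculation asks for 64 patients in each arm. The aim given there is "to statistically detect a minimum effect size of *d* = 0.5 between mean BCTQ scores of both groups". Alpha is 5% (two-sided) and power 80%. On recruitment the section states: "A total of 200 patients will be included (100 patients per treatment arm), taking into account possible drop-out". No SD and no covariate correlation is stated.

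**Reproducing the plan's figure.** The normal approximation, n = 2(z₀.₉₇₅ + z₀.₈₀)²/d² with d = 0.5, gives 63 per arm. The two-sample t-test gives 63.77, so 64 per arm, with power 0.801 at 64. The stated figure reproduces and assumes no gain from any covariate.

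**Effect of adding PHQ-4.** Let r be the partial correlation of T0 PHQ-4 with the 12-month BCTQ, given the baseline BCTQ. The document does not state it; 0.1 to 0.3 is an assumption. Adding PHQ-4 multiplies the residual SD by √(1 − r²). As a simplification, d = 0.5 is taken to be standardised by the SD before PHQ-4 is added, so it becomes 0.5/√(1 − r²).

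| r | Variance saved (r²) | SE reduction, 1 − √(1 − r²) | n per arm for 80% power | Power at 64 per arm |
|---|---|---|---|---|
| 0 | 0 | 0 | 64 | 0.801 |
| 0.1 | 1% | 0.5% | 64 | 0.805 |
| 0.2 | 4% | 2.0% | 62 | 0.817 |
| 0.3 | 9% | 4.6% | 59 | 0.837 |

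At 100 per arm with no drop-out, power is 0.940 without PHQ-4 and 0.943 to 0.958 with it over the same range.

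**Is 0.1 to 0.3 a sensible range?** Suppose PHQ-4 correlates c with BCTQ at every visit, and BCTQ at baseline and 12 months correlate ρ. Then

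r = c(1 − ρ)/√[(1 − c²)(1 − ρ²)].

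With c = 0.3 and ρ = 0.5, r = 0.15/√(0.91 × 0.75) = 0.182, so 3.3% of the variance is saved. With c = 0.3 and ρ from 0.7 down to 0.3, the saving is 1.7% to 5.3%. With c from 0.2 to 0.5 and ρ from 0.3 to 0.7, r runs from 0.09 to 0.42. Both c and ρ are assumed.

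**With the 3- and 6-month outcomes also in the model.** Use the same illustration (c = 0.3, all BCTQ correlations 0.5) and condition on three BCTQ measurements:
- remaining covariance: 0.3 × [1 − 3(0.5)/(1 + 2 × 0.5)] = 0.3 × 0.25 = 0.075
- remaining BCTQ variance: 1 − 3(0.25)/2 = 0.625
- remaining PHQ-4 variance: 1 − 3(0.09)/2 = 0.865
- r = 0.075/√(0.625 × 0.865) = 0.102, so about 1.0% of the variance is saved, against 3.3% with baseline BCTQ alone.

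**Chance imbalance is the same quantity.** In residual SD units the variance of the unadjusted difference is 2/n. It splits into r²(2/n), due to imbalance in PHQ-4, and (1 − r²)(2/n). At 100 per arm and r = 0.2 the first part is 0.04 × 0.02 = 0.0008, a standard deviation of 0.028 SD. This is exactly the 4% in the table, not an addition to it.

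**The case against.** The strongest case against the point is that nothing in the article is wrong here. It never promises PHQ-4 in the treatment model. Under randomisation the comparison is unbiased and its type I error valid without it, and no stated figure relies on it. Distress has its own tertiary analysis, and the Discussion itself calls research into its effect on treatment outcome limited. The gain rests on an assumed correlation. The association the article cites is with BCTQ scores themselves, and baseline BCTQ is already a covariate. In the WHOQOL-BREF model the baseline score already contains a psychological domain. All of this stands, and it limits the point to an optional refinement. It does not remove it, because the list is explicitly fixed for a purpose that PHQ-4 serves and the cost is close to nil.

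A reader might infer three stronger things that the document does not support:
- **That chance imbalance in distress is a second harm beside lost precision.** It is random error that the confidence interval already covers.
- **That the open-label design makes the omission worse.** Adjusting for baseline PHQ-4 does nothing about unblinded self-report.
- **That adding PHQ-4 would test the hypothesis of a lower treatment effect.** A main-effect covariate does not.

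The same sentence of the plan also adjusts for the 3- and 6-month outcomes, which arise after randomisation. That is a separate and more serious matter, which this point does not settle.

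**Conclusion.** The point holds as a minor improvement. Baseline PHQ-4 is collected before allocation is known, fits the declared purpose of the covariates, and is left out of the list. The omission biases nothing and changes no stated power figure.

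Under an assumed partial correlation of 0.1 to 0.3 given baseline BCTQ, the standard error would fall by 0.5% to 4.6%. Up to 0.2 the gain in power at 64 per arm is under 2 percentage points (0.801 to 0.817); a material gain needs about 0.3 or more, and the document gives no coefficient to support that. With the 3- and 6-month outcomes retained, the gain is likely smaller still. The facts about the covariate list are certain; the size of the benefit is not.

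**What to change.** In Planned analyses, and in the matching sentence of the Abstract, add the T0 PHQ-4 total score as a fixed baseline covariate in the BCTQ model. For consistency, do the same in the WHOQOL-BREF, absenteeism and resource-use models, which share the list. Use only the T0 value: PHQ-4 at V1, V2 and T1 to T3 is measured after randomisation and should not enter. Specify this before outcome data are compared by arm. Keep the separate tertiary analysis of distress, since the covariate does not replace it. If the sponsor prefers to leave PHQ-4 out, one sentence giving the reason would do.

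The cost is one line of wording and one degree of freedom per model, with no new data.
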